### Sample Size

Physicians in the pediatric ED see on average 900 patients over 3 months. Assuming an intraclass correlation of 0.1 in time between delivery of the laboratory results and the caregiver accessing them, 5253 individual patients are required to have a 90% chance of detecting, as significant at the 5% level, a decrease in a time difference of 0.5 SD. This represents approximately 18 physicians including 100 patients per month over 3 months. In order to obtain 18 physicians, we will recruit physicians over 2 consecutive rotation periods.

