### Participants

Eligible participants will be postgraduate residents pursuing a less than 6-year residency in pediatrics, pediatric emergency medicine fellows, and registered nurses from the pediatric ED (aged >18 years). Written informed consent will be obtained from each participant in the experimental group after full information disclosure prior to study participation. On the first day, after completing the informed consent form, participants will be asked to download the app to their personal smartphone through the secure institutional Microsoft Intune portal (Microsoft Corporation). They will then be required to attend a unique standardized 5-minute introduction course to the app and its functionality by the study investigators, but they will not receive specific instructions on how often to use the app. The participants will remain the same throughout the intervention period. No one will be asked to advise on the interpretation of the results.

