The usual number of residents is 10 on a monthly basis during a 4-month period. They provide coverage for 6-7 overlapping shifts, which begin at different times, with each shift ranging from 10 hours (9 hours of patient care, 1 hour of recovery) to 12 hours (12 hours of patient care, no recovery time at night) on weekdays and 6 shifts on weekends to cover a 24-hour day (Table 1). During the intervention schedule, residents typically work 3-4 night shifts followed by 72 hours off, then 3-5 consecutive day shifts before 2 days off, followed by 2-day shifts. This pattern repeats throughout the month, with occasional additional days off or vacations. The 14 fellows (some of whom are part-time) work in an irregular combination of 6 overlapping 8-12 hour shifts on weekdays and 3 shifts on weekends (Table 1). Finally, 17 nurses out of a total of 43 cover a 24-hour day. This represents a total coverage of 70-78 hours, 30-48 hours, and 102 hours per day for residents, fellows, and nurses, respectively. The ED uses the Canadian Triage Acuity Scale [21] to guide patient treatment based on medical-surgical urgency. On average, each resident sees about 300 patients per month and fellows 50-70, with a ratio of medicine: surgery-trauma cases of 2/3:1/3. The standard physician-to-patient ratio ranges from 1:5 to 1:7 and varies according to disease acuity and time of the visit. The nurse-to-patient ratio ranges from 1:3 to 1:5. Caregivers see patients on a first-view [22], on-site, 24/7 basis. Whether they work 8-, 10-, or 12-hour shifts, they all work in the same area, have access to the same patient volume, and see the same patient complaints. They have full, secure 24/7 electronic access to laboratory results.

**Table 1 table1:** Work shifts by time of day and occupation.

Caregiver and work shift		Count, n	
		Weekdays	Weekend

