### Statistical Analysis

The association of app use with the time between delivery of the laboratory results and their access by caregivers will be assessed using generalized estimating equations with an exchangeable correlation structure to account for the nested structure of the outcome (ie, time) within the physicians. To account for potential differences in case-mix and physician characteristics, we will use multivariable generalized estimating equations. The covariates will be as follows: (1) the triage acuity scale, (2) type of pathology (medical, surgical-traumatological, psychiatric), (3) experience of the caregiver expressed in years since certification, (4) patient age, (5) patient sex, (6) workload represented by the number of patients present in the emergency room, (7) time of day or night, (8) day of the week, and (9) month of the year (seasonal variability). To account for the possible effect of exogenous factors that would impose an asymmetry in the data (skewness on the right) by extending the awareness of laboratory results, we will identify these factors as the study progresses prospectively and take them into account in the final analysis. The same analyses will be performed for the nurses. We will carefully monitor and evaluate through descriptive analyses any differences between nurses’ and physicians’ frequency access to laboratory results. If the target sample size cannot be reached, we will first extend the prospective data collection period by 3 months (deemed ethically acceptable as not impacting patients) or present only the results of qualitative user experience interviews.

For the technology acceptance self-administered survey questionnaire, scores on the 8 technology acceptance constructs will be described using descriptive statistics. Items on the SUS questionnaire will be described using frequencies. Analyses will be carried out using R software (R Core Team) [27]. All statistical tests will be 2-sided, with an α risk of .05.

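### The target of 5253 patients (18 physicians) is a two-period total sought in the prospective period alone, and the extension and fallback rule relies on it without naming unit or period.

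*Protocol article*

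**What the plan says.** The Sample Size section of the protocol article assumes an intraclass correlation of 0.1 in the time to access results and states that "5253 individual patients are required to have a 90% chance of detecting, as significant at the 5% level", an effect of 0.5 SD. It equates this with about 18 physicians, each including 100 patients per month for 3 months, and continues: "In order to obtain 18 physicians, we will recruit physicians over 2 consecutive rotation periods".

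Only the app period recruits anyone. The Participants section describes consent for the experimental group, and the Procedure and Intervention section takes the control period from 12 months of retrospective records.

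The Statistical Analysis section says that if the target sample size is not reached, prospective collection will first be extended by 3 months, or only qualitative user interviews will be presented. It does not say whether the target is 5253 patients or 18 physicians, or which period it counts.

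On who takes part, the Participants section says "The participants will remain the same throughout the intervention period", while the Setting section says "The usual number of residents is 10 on a monthly basis during a 4-month period".

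**The concern.** A sample size that sums two groups has been turned into a recruitment goal for one of them. That alone would only make the study larger than its own inputs require. It matters because a decision rule depends on the figure. Read literally, the rule could prolong data collection, or replace the primary comparison with qualitative interviews, when the physicians already enrolled give the planned power. The prescribed remedy, more months, mainly adds patients per physician, which is the quantity that contributes least at this intraclass correlation. Whether an extension could also bring in new physicians depends on two statements that do not agree: a fixed set of participants, and recruitment over two rotations.

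**Working it through.** **Inputs.** From Sample Size: effect 0.5 SD, power 90%, significance level 5%, intraclass correlation 0.1, 300 patients per physician (100 x 3 months). From Statistical Analysis: "All statistical tests will be 2-sided, with an α risk of .05". The allocation ratio is not stated; 1:1 is assumed because it reproduces the figure.

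**Reproducing 5253.**
- Per group, unclustered: 2 x (1.96 + 1.2816)² / 0.5² = 84.06, rounded up to 85.
- Design effect: 1 + (300 - 1) x 0.1 = 30.9.
- Two groups: 2 x 85 x 30.9 = 5253.0, an exact match.
- One group: 85 x 30.9 = 2626.5, which does not match. Nor does a one-sided total (4264), or a total with 100 or 900 patients per physician (1853 or 15,453).

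So 5253 is the total over both periods: 5253 / 300 = 17.5 physicians, or 2626.5 / 300 = 8.76, about 9, per period.

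**Power by number of physicians.** For k physicians with m patients each, the variance of a period mean in SD² units is (1 + (m - 1) x 0.1) / (k x m). The check takes equal numbers in both periods, different physicians before and after, and either a normal or a t reference with 2k - 2 degrees of freedom.

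| Physicians x patients, per period | Patients per period | Power, normal | Power, t |
|---|---|---|---|
| 9 x 300 | 2700 | 91% | 87% |
| 10 x 300 | 3000 | 94% | 91% |
| 18 x 50 | 900 | 99% | 99% |
| 18 x 300 | 5400 | 99.7% | 99.5% |

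For 10 x 300, the standard error is √(2 x 30.9 / 3000) = 0.1435, and 0.5 / 0.1435 = 3.48.

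**The rule applied to these cases.** Ten prospective physicians with 300 patients each miss the target in either unit (3000 against 5253, 10 against 18), yet power is 91% on the t reference. Eighteen physicians with 50 patients each meet the physician count and miss the patient count, with power about 99%. Ten physicians for 6 months at 100 per month give 10 x 600 = 6000 patients, so they meet the patient count and miss the physician count.

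**What an extension adds.** Effective sample size for ten physicians is 6000 / 60.9 = 98.5 after 6 months and 9000 / 90.9 = 99.0 after 9 months. With equal groups, t-based power moves from 91.3% to 91.4%. One physician can never contribute more than about 1 / 0.1 = 10 effective patients.

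**The case against.** The strongest reply is that nothing has been miscalculated: 5253 is correct for its inputs, and the text at once gives the physician equivalent and recruits in physicians. The slip also errs on the safe side. All of this stands. It limits the point to how the figure is used; it does not settle what the extension rule counts.

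Four stronger readings are tempting but not supported.

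- A reader might infer that power is only 87%, from 9 against 9 on a t reference. That is the split implied by the formula, not the recruited design, which seeks 18 prospective physicians against 12 months of records.
- A reader might infer that patient count has no relation to power, since 6 x 900 = 5400 per period would meet the target with 78% (normal). But more patients per physician do help a little, a larger control group narrows the shortfall (6 x 876 against 18 x 300 gives 91%), and nothing suggests so few physicians. Besides the ten residents, the Setting section counts 14 fellows, who are eligible.
- Two 4-month rotations might seem not to fit a 6-month window. Each physician needs only 3 months, and the article does not require complete rotations.
- With few physicians, the analysis "using generalized estimating equations with an exchangeable correlation structure" might be thought to inflate type I error. The article does not name the variance estimator or reference distribution, and an analysis plan commonly settles these.

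An extension could also bring in new residents, which would add real power. That depends on which statement about participants governs.

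**Conclusion.** The point holds as one about the target and the rule attached to it. The figure of 5253 patients, or 18 physicians, is the requirement for both periods together, while the plan seeks all 18 in the prospective period. The text does not say outright that 5253 is a prospective count, but its recruitment and extension sentences leave little other reading. The consequence is overshoot: with 18 physicians of 300 patients in each period, power is above 99%. The risk is an unnecessary extension, or the loss of a quantitative comparison that already has about 90% power, together with an extension that adds almost nothing if the physicians stay the same.

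These figures assume 1:1 groups, equal patients per physician, different physicians before and after, and the stated intraclass correlation. The number of pre-period physicians is not stated; more of them would raise power for any given prospective number. If some physicians contribute to both periods, fewer would be needed.

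**What to change.** 1. Restate the target as physicians per period: about 9 by the normal formula, or 10 with a t reference, for 90% power at 0.5 SD with 300 patients each. Alternatively, if 18 prospective physicians are intended, say so and give the power this provides against the stated number of pre-period physicians.
2. Tie the extension and the qualitative-only fallback to that prospective physician count, not to 5253 patients, and say whether an extension enrols new physicians.
3. Reconcile the statement that participants stay the same with recruitment over two rotations, for example by limiting it to within a rotation if that is what is meant.

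The cost is a restated figure and a few sentences. No additional patients, data or analyses are required.

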### Statistical Analysis

The association of app use with the time between delivery of the laboratory results and their access by caregivers will be assessed using generalized estimating equations with an exchangeable correlation structure to account for the nested structure of the outcome (ie, time) within the physicians. To account for potential differences in case-mix and physician characteristics, we will use multivariable generalized estimating equations. The covariates will be as follows: (1) the triage acuity scale, (2) type of pathology (medical, surgical-traumatological, psychiatric), (3) experience of the caregiver expressed in years since certification, (4) patient age, (5) patient sex, (6) workload represented by the number of patients present in the emergency room, (7) time of day or night, (8) day of the week, and (9) month of the year (seasonal variability). To account for the possible effect of exogenous factors that would impose an asymmetry in the data (skewness on the right) by extending the awareness of laboratory results, we will identify these factors as the study progresses prospectively and take them into account in the final analysis. The same analyses will be performed for the nurses. We will carefully monitor and evaluate through descriptive analyses any differences between nurses’ and physicians’ frequency access to laboratory results. If the target sample size cannot be reached, we will first extend the prospective data collection period by 3 months (deemed ethically acceptable as not impacting patients) or present only the results of qualitative user experience interviews.

For the technology acceptance self-administered survey questionnaire, scores on the 8 technology acceptance constructs will be described using descriptive statistics. Items on the SUS questionnaire will be described using frequencies. Analyses will be carried out using R software (R Core Team) [27]. All statistical tests will be 2-sided, with an α risk of .05.

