### Procedure and Intervention

This is a pre-post study. Before the implementation of the app, EMR-based data from the past 12 months will be collected retrospectively. These data will include the times (ie, HH:MM:SS) that results issued by the central laboratory were available on the institutional EMR as well as the times at which these results were accessed by caregivers through conventional computerized workstations. After the implementation of the app, data will be collected prospectively over a 6-month period of use. This will include the times (HH:MM:SS) when the results issued by the central laboratory are made available through the app on caregivers’ smartphones and access times as well as concurrent or preferred access times on the conventional computerized workstations should this occur. Individual acceptance of the app on the first day (a priori) and then on the last day of the intervention will be evaluated through the Unified Theory of Acceptance and Use of Technology (UTAUT) [23]. Usability of the app will be measured by the System Usability Scale (SUS) [24]. Figure 1 shows the study procedure, and Table 2 presents the study schedule. Use of the app will be on a 24-hour basis and at the discretion of participants.

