### Data Collection

Electronic data will be extracted from the institutional data lake. The data lake stores all data and events from the EMR information system in a database and can be retrieved using Simple Protocol and RDF Query Language (SPARQL) queries. In the preintervention period, the time stamp of the laboratory results on the EMR will be identified as the time of issuance of the said results. Access to these results by the physicians and nurses will be defined by the time stamp of the first access to the laboratory results’ viewer on the EMR. Access to results on the app will be computed either by the time stamp of the push notification access or to the dedicated page on the app. No other patient-level data such as identifiers or clinical characteristics will be collected. Collected data will be transmitted to the REDCap database web app (REDCap, Vanderbilt University) hosted by the hospital for analysis.

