### Blinding

Although neither the participants nor the study investigators can be blinded to the intervention, both will be blinded to the results of the study until their final analysis by the statistician. Participants will be informed only of the overall purpose of the study, which is to evaluate the effects of the app on quality of care, but not about the aim of reducing the time to access laboratory results in order to minimize bias. The statistician will remain blinded to allocation until the final analysis.

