## Results

Retrospective laboratory data will be arbitrarily collected from October 31, 2021, to October 31, 2022. Prospective data will be collected from the start of enrollment on November 1, 2022, through April 30, 2023. We anticipate an analysis of the results by mid-2023 and expect the results to be published in late 2023.

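### Factors that lengthen time to access are left open and identified only during the app period, with no rule for finding them in the control year

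*Protocol article*

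**What the plan says.** The primary outcome is a mean time in minutes from release of a laboratory result to its being accessed, before and after the app (Primary Outcome). The Statistical Analysis section specifies generalized estimating equations with nine named covariates, among them workload, time of day, day of week and month. It then turns to right skew. The aim is stated as "To account for the possible effect of exogenous factors that would impose an asymmetry in the data (skewness on the right"), meaning factors that delay awareness of results, and the method is that "we will identify these factors as the study progresses prospectively and take them into account in the final analysis".

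The two periods are observed differently. For the control year, "EMR-based data from the past 12 months will be collected retrospectively" (Procedure and Intervention). The dates are in Results: "Retrospective laboratory data will be arbitrarily collected from October 31, 2021, to October 31, 2022", and then "Prospective data will be collected from the start of enrollment on November 1, 2022, through April 30, 2023".

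The Blinding section concedes that "neither the participants nor the study investigators can be blinded to the intervention". The same sentence adds that participants and investigators stay blinded to the study results until the final analysis. It also says: "The statistician will remain blinded to allocation until the final analysis".

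**The concern.** This is a stated rule for the primary analysis, not a detail left to another document. It has three weaknesses.

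- The class of factors is open. It is defined by its effect on the outcome (longer times), and the article does not say whether a factor will enter as a covariate, an exclusion or something else.
- The factors are noticed while the app is in use. The control year is already closed by then, and nothing requires a search for the same factors in it.
- The rule looks only for factors that lengthen times, in an outcome summarised by a mean, where long times carry most weight.

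If post-period delays are explained and identical pre-period delays are left in, the app appears to shorten access times even when it does nothing. The study is unrandomised and compares calendar periods, so no other design feature would offset such an imbalance.

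**Working it through.** **1. The plan's own figure.** Inputs from Sample Size: difference 0.5 SD, two-sided 5%, power 90%, intraclass correlation 0.1, and 100 patients per month over 3 months, so 300 per physician.

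- Per group without clustering: 2 × (1.960 + 1.282)² / 0.5² = 84.1, rounded up to 85; total 170.
- Design effect: 1 + (300 − 1) × 0.1 = 30.9.
- Total: 170 × 30.9 = 5253, as stated; 5253 / 300 = 17.5, about 18 physicians.

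The sample size reproduces exactly and is not affected by this point. It also supplies a standard error for the next steps. With two equal groups, SE = √(30.9 × 4 / 5253) = 0.153 SD. The equal split is that of the sample-size calculation; the actual periods are 12 and 6 months, so this SE is illustrative.

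**2. Bias from one-sided flagging.** Let a share f of results in both periods be hit by a factor that adds a mean delay D (in SD of the times without the factor), and let the app have no effect. If the factor is flagged and adjusted for only after implementation, the post-period mean loses its f × D while the pre-period mean keeps it. The estimated difference is then 0 − f × D = −f × D. The result is the same if flagged post-period results are excluded instead of adjusted for.

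**3. False-positive rate.** With b = −f × D, the two-sided rejection rate is Φ(−1.96 − b/SE) + 1 − Φ(1.96 − b/SE). For b = −0.10, b/SE = −0.652, giving Φ(−1.308) + Φ(−2.612) = 0.0954 + 0.0045 = 0.0999. The values of f and D are assumptions; the documents give none.

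| f | D (SD) | Bias (SD) | Share of 0.5 SD | Two-sided rejection, no app effect |
|---|---|---|---|---|
| 2% | 2 | −0.04 | 8% | 5.8% |
| 5% | 2 | −0.10 | 20% | 10.0% |
| 5% | 3 | −0.15 | 30% | 16.5% |
| 10% | 2 | −0.20 | 40% | 25.6% |

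**4. Check by simulation.** Two groups of 9 physicians with 292 patients each, intraclass correlation 0.1 and no app effect were simulated 300 times per case. Flagging the factor only in the post period moved the estimate by −0.0998 (5%, 2 SD), −0.1998 (10%, 2 SD) and −0.1503 (5%, 3 SD). Flagging it in both periods moved it by +0.0004, +0.0003 and −0.0006. Symmetric handling therefore removes the bias.

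**The case against.** The strongest reply is that the text says where factors are identified, not that only post-period records are adjusted. The final analysis covers both periods, and a factor noticed in the app period could be traced back. The data lake is said to hold all events from the record system, so outages could be recovered from logs. Busy nights are largely covered already by the workload and time-of-day covariates. This stands: one-sided adjustment is something the rule permits, not something it prescribes.

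A reader might also infer that factors will be chosen after the data are seen. The documents do not say so, and the Blinding section keeps investigators blind to results. That protection lessens the risk without removing it. Investigators know when the app is in use, and they would have to recognise causes of long delays while the study runs. The statistician's blinding to allocation is weak, because allocation is calendar period and app time stamps exist only after implementation.

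A third inference would be that long times will be cut from the post period. Dropping the slowest 2% to 5% there alone would lower a log-normal mean by 9% to 29%, or 0.09 to 0.17 SD (log-SD assumed 0.8 to 1.2). The article proposes no trimming, and coming straight after a covariate list, the phrase reads more naturally as covariate adjustment. Those figures therefore do not measure what the plan will do.

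Finally, the Data Collection section states: "No other patient-level data such as identifiers or clinical characteristics will be collected". This may limit tracing patient-level causes in the control year, but it would not block system-level or calendar-level factors. It also sits awkwardly with some listed covariates, which is a separate matter.

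**Conclusion.** The point holds as a risk created by an open rule. The factors are undefined and identified only in the app period, and nothing requires the same search in the control year. If a factor acts in both periods and is flagged in one, the bias is −f × D, which favours the app. Over the assumed cases this is 0.04 to 0.20 SD, or 8% to 40% of the planned effect, with the false-positive rate between 5.8% and 25.6%. At the low end the effect is small.

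The direction is not a given. If a factor truly occurs only after implementation, adjusting for it removes confounding. The documents do not support saying that the plan adjusts one side or that the result will favour the app. They support saying that nothing in the rule prevents it.

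**What to change.** Replace the sentence in Statistical Analysis so that:

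- the model with the nine listed covariates is the primary analysis, with no removal of long times;
- any further factor (for example, system-outage intervals from logs) is defined before unblinding, is retrievable by the same rule in both periods, is applied identically to both, and is reported as a sensitivity analysis;
- right skew is addressed by one pre-specified sensitivity model, for example generalized estimating equations with a log link, which gives a ratio of mean times.

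The choice of skew model is open, provided it is fixed in advance. Disruptions during the app period can still be logged and described. The same wording should govern the nurses' analysis. The cost is two sentences and one additional model.
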